## Abstract

**Background:**

Hematopoietic stem cell transplantation is an intensive therapy used to improve survivorship and cure various oncologic diseases. However, this therapy is associated with high mortality rates and numerous negative side-effects. The recovery of the immune system is a special concern and plays a key role in the success of this treatment. In healthy populations it is known that exercise plays an important role in immune system regulation, but little is known about the role of exercise in the hematological and immunological recovery of children undergoing hematopoietic stem cell transplant. The primary objective of this randomized-controlled trial (RCT) is to study the effect of an exercise program (in- and outpatient) on immune cell recovery in patients undergoing an autologous stem cell transplantation. The secondary objective is to determine if an exercise intervention diminishes the usual deterioration in quality of life, physical fitness, and the acquisition of a sedentary lifestyle.

**Methods:**

This RCT has received approval from The Conjoint Health Research Ethics Board (CHREB) of the University of Calgary (Ethics ID # E-24476). Twenty-four participants treated for a malignancy with autologous stem cell transplant (5 to 18 years) in the Alberta Children’s Hospital will be randomly assigned to an exercise or control group. The exercise group will participate in a two-phase exercise intervention (in- and outpatient) from hospitalization until 10 weeks after discharge. The exercise program includes strength, flexibility and aerobic exercise. During the inpatient phase this program will be performed 5 times/week and will be supervised. The outpatient phase will combine a supervised session with two home-based exercise sessions with the use of the Wii device. The control group will follow the standard protocol without any specific exercise program. A range of outcomes, including quantitative and functional recovery of immune system, cytokine levels in serum, natural killer (NK) cells and their subset recovery and function, and gene expression of activating and inhibitory NK cell receptors, body composition, nutrition, quality of life, fatigue, health-related fitness assessment and physical activity levels will be examined, providing the most comprehensive assessment to date.

**Discussion:**

We expect to find improvements in immunological recovery and quality of life, and decreased acquisition of sedentary behavior and fitness deconditioning. The comprehensive outcomes generated in this RCT will provide preliminary data to conduct a multisite study that will generate stronger outcomes.

**Trial registration:**

Gov identification # NCT01666015

## Background

Hematopoietic stem cell transplantation (SCT) is an intensive therapy used in the treatment of various oncologic diseases [1]. This treatment has improved survivorship in recent years, but is associated with numerous negative physical and psychological side-effects as well as a spectrum of late effects [1-5]. Oeffinger et al. reported that one-third of childhood cancer survivors have severe or life-threatening medical complications 30 years after diagnosis, and those who received SCT compound the high-risk group [5]. Recent research attention has been focused on diminishing the impact of these potential negative side-effects and late-effects thereby, improving the quality of life (QOL) of pediatric cancer survivors.

There is increasing evidence that exercise (EX) is safe, beneficial and feasible in different stages of cancer treatment [3-6], including in immune-compromised patients [7]. However, scientific evidence suggests that children with cancer are more sedentary than their healthy peers [8,9]. It has been argued that childhood cancer survivors are subject to an insidious “spectrum of disuse” as a result of an overly cautious approach towards EX, fostered by concerned parents and environmental factors [10]. A potential explanation for this overprotective attitude may stem from a general lack of education about what a child can be expected to do after cancer treatments [11].

Huang et al. [3] in a recent review showed that the impact of EX on health and physical function in pediatric oncology is promising. However, only 15 published studies (1993-2011) have examined EX as an intervention [3]. Of these 15, only 4 were RCTs, and only 3 studied the effect of EX on immunological function [7,12,13]. Overall, these 3 studies found that EX was beneficial and did not impair immune system recovery in any way that could provoke concern for health. Furthermore, Chamorro et al. [7] showed that EX was safe in neutropenic patients, who were also able to avoid weight lost during hospitalization. This previous research is limited by small sample size and limited immunological analyses, including no assessment of NK cell function or cytokine environment. In addition, most of the previous EX interventions were in acute lymphoblastic leukemia patients undergoing maintenance therapy [3]. To our knowledge, only three English language publications described the effect of EX in children with cancer undergoing SCT [7,14,15]. These articles suggest that EX is safe, feasible and has a promising role in the recovery of children undergoing SCT.

Despite robust scientific evidence describing the positive effects of EX in the adult cancer population, limited research efforts have focused on exploring the translation of EX therapy to children. Specifically, the role of EX in the immune system recovery of pediatric patients undergoing SCT has not been examined sufficiently to date, however the results from the adult population [16-18] are promising. It is argued that improved QOL through an EX program is sufficient rationale to providing EX programming. However EX will be further supported if it can be shown to improve immune system recovery which may result in diminished risk of infection, hospitalization days and improve overall survival. This RCT will significantly add to the evidence on the effect of EX on the recovery of children undergoing SCT. A range of outcomes, including quantitative and functional recovery of immune system, e.g., different leukocyte cell subset counts in peripheral blood, cytokine levels in serum, NK cells and their subset recovery and function, and gene expression of activating and inhibitory NK cell receptors known as Killer Immunoglobulin like Receptors (KIR), body composition, nutrition, QOL, fatigue, health- related fitness assessment and physical activity levels will be examined, providing the most comprehensive assessment to date.

The purposes of the present study are:

### Primary

Study the effect of an EX program (in- and outpatient) on immune cell recovery in patients undergoing an autologous SCT.

### Secondary

Determine if an EX program performed in patients undergoing autologous SCT diminishes the deterioration of physical fitness, physical activity levels and improves QOL.

### Tertiary

Establish the program’s feasibility (uptake and adherence) to provide the impetus to run multi-centre research with larger populations in the future.

## Methods

### Study design

SCORE “Stem Cell patients Ongoing Recovery through Exercise” is a RCT of pediatric cancer patients undergoing autologous SCT. Assessors will be blind to participant’s condition (EX or control) and all the statistical analyses will be performed maintaining blindness to condition. Blinding of assessors and statistical analyses ensures limited bias on outcomes, especially with subjective outcomes of interest. Flow through the study is depicted in Figure 1.

**Figure 1 F1:**
[figure not shown]
Participants flow through SCORE study.

This study will examine the effect of two phases of an EX program on several health related outcomes in pediatric patients undergoing autologous SCT (Figure 2). The first phase of the EX program will be an inpatient intervention, beginning when the child is hospitalized undergoing conditioning therapy and continuing until discharge.

**Figure 2 F2:**
[figure not shown]
SCORE study protocol.

The second phase will be a 10-week outpatient intervention, beginning once the child is discharged. We will utilize a mixed EX program, including supervised (at the University of Calgary) and home-based training incorporating the use of the Nintendo ® Wii device™ (Wii Fit, Wii Dance and Sports™ games).

Assessments include measures of QOL, fatigue, health-related fitness (HRF), physical activity levels and hematological and immunological reconstitution. Assessments will be completed at baseline, 30, 85 and 180 days post infusion day (day 0+). Hematological and immunological reconstitution will be assessed at the time points described above, plus at 7, 15 and 56 days post reinfusion. The baseline assessment will be completed within the two-month period prior to the conditioning regimen. The 30 day assessment is intended to capture the effect of Phase 1, the EX program during the hospitalization period (from conditioning regimen up to discharge). The 85 day assessment is intended to capture the early survivorship recovery period after an autologous SCT and the effect of Phase 2, EX program during the outpatient phase. The 180 day assessment will provide a mid-term follow-up of physical activity, QOL, fatigue and hematological and immunological reconstitution. These outcomes will allow us to examine the impact of an EX program implemented early during the SCT process 3 months after finishing the EX intervention on (i) physical activity levels (ii) QOL and fatigue iii) hematological and immunological recovery

### Study population

A total of 24 children will be recruited for this RCT; 12 patients will be assigned to an EX training program and 12 subjects will be assigned to a control group (without any specific training). A sequence to allocate participants randomly will be generated by the software Research Randomizer, a research tool provided by the Social Psychology Network (http://www.socialpsychology.org). Allocation concealment will be ensured. After baseline assessments each participant will choose a sealed, non transparent envelop, which contains a number that will allocate the subjects to the control or EX group. The research coordinator will be responsible for the random allocation.

Eligibility criteria includes: (1) autologous SCT at Alberta Children’s Hospital (ACH) for malignancy, (2) age 5 to 18 years of age, (3) will be receiving myeloablative conditioning regimen, (4) no evidence of cardiac or pulmonary failure associated with treatment (shortening fraction (SF) ≥28%, ejection fraction (EF) ≥ 50%), (5) no functional nor cognitive limitation that would prohibit performance of the home-based training, (6) approval by treating oncologist for participants, (7) a parent or legal guardian must sign the consent form, and (8) children should express verbal assent to participate. The entire team of assessors and the persons performing the statistical analyses will be blinded to group assignment.

### Recruitment

Children undergoing autologous SCT will be recruited through the Section of Pediatric Oncology and Blood and Marrow Transplantation at ACH. ACH is the SCT centre for Alberta. The referring oncologist will identify potential subjects and the research nurse will contact them to present the study at least 4 weeks before the hospitalization to start autologous SCT treatment. Those subjects who are interested in the study will be asked to sign the consent form by the research nurse and will be contacted by the research assistant to set up the baseline assessment.

This on-site patient recruitment method will be more likely to enhance recruitment efforts than a mail out or other off-site method. Also, prospective subjects might feel more supported if the physician supports the research protocol. In order to obtain a homogenous sample, is known that the recruitment phase will take between 2-3 years to reach the sample described.

### Intervention and control group

#### Intervention group

Children in the intervention group will participate in an inpatient and outpatient mixed EX program including both resistance and aerobic training.

#### Control group

These subjects will not participate in any scheduled EX and will perform the same battery of tests as the intervention group. They will be offered an EX program upon completion of phase 2, to be held in the Thrive Centre, University of Calgary.

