## Discussion

The primary focus of the SCORE study will be to identify the effect of an early EX intervention in the immune system recovery of pediatric patients undergoing autologous SCT. Other important health outcomes will include the intervention impact on QOL and fatigue. We will also be able to examine the mediators and moderators of any observed associations between PA, HRF, and health outcomes after SCT at a mid-term assessment point. Finally, we will be able to identify if an early intervention will be able to diminish the acquisition of a sedentary lifestyle,

Taken together, these data will provide a detailed and complete understanding of the effect of an EX program in pediatric cancer patients undergoing autologous SCT. From our knowledge, this study will be one of the most comprehensive studies in this population, and will provide an initial database along with the impetus to promote a multisite study. A multisite study is the ideal approach to examine the impact of EX on immunological and patient-reported outcomes in the pediatric oncology population, due to relatively small sample sizes at any one centre.

The SCORE study is designed to address the following research themes through pilot data:

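### Controls are offered exercise about three months before day 180, so the day-180 contrast may become early versus optional delayed exercise

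*Protocol article*

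**What the plan says.** Until the offer, the control condition is clear: "These subjects will not participate in any scheduled EX and will perform the same battery of tests as the intervention group". The next sentence of the Control group section then changes it: "They will be offered an EX program upon completion of phase 2, to be held in the Thrive Centre, University of Calgary".

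The text after Figure 2, under Study design, fixes the timing. On length and start: "The second phase will be a 10-week outpatient intervention, beginning once the child is discharged". On the visit that belongs to this phase: "The 85 day assessment is intended to capture the early survivorship recovery period after an autologous SCT and the effect of Phase 2". On the last visit: "The 180 day assessment will provide a mid-term follow-up of physical activity, QOL, fatigue and hematological and immunological reconstitution". The purpose of that last visit is to "examine the impact of an EX program implemented early during the SCT process 3 months after finishing the EX intervention".

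The Data analysis section plans doubly multivariate repeated measures ANOVA to compare intervention with control for the primary and secondary objectives. It does not treat day 180 differently from the other visits. The Discussion expects a further result: "Finally, we will be able to identify if an early intervention will be able to diminish the acquisition of a sedentary lifestyle".

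**The concern.** A follow-up visit some months after an intervention has ended tests whether its effect lasts. That works only if the comparison arm is still in its original condition. Here the comparison arm may begin exercising at the point where the follow-up interval starts, while the intervention arm has finished its programme. The two statements sit in different sections of the article and are not reconciled.

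What is at stake is the mid-term conclusion on physical activity, quality of life, fatigue and immune recovery. A small day-180 difference could mean that the early benefit faded, or that controls caught up through their own exercise. The arm comparison alone could not tell these apart. Any repeated-measures test that includes day 180 carries the same ambiguity.

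**Working it through.** **1. The plan's own interval.** The plan places day 180 "3 months after finishing the EX intervention". Day 85 is the phase 2 assessment, so 180 − 85 = 95 days, which is 95/7 = 13.6 weeks, or about 3.1 months. The stated interval is reproduced.

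**2. When the offer opens.** Controls have no phase 2 of their own, so I read its completion as the matching time, 10 weeks after discharge. The day of discharge is not given; I assume day 10 to day 30 after infusion.

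- End of phase 2 = discharge day + 70
- Time left before day 180 = 180 − (discharge day + 70)

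| Discharge (assumed) | Phase 2 ends | Days left to day 180 |
|---|---|---|
| day 10 | day 80 | 100 |
| day 15 | day 85 | 95 |
| day 20 | day 90 | 90 |
| day 30 | day 100 | 80 |

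In every row the window is longer than 70 days. The length of the programme offered to controls is not stated. If it matched the outpatient phase and began promptly, a control could complete it before day 180. With a later start, the control could still be in it at that visit.

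**3. Which visits are exposed.** Days 7, 14 or 15, 30 and 56 all come before the offer. With discharge on day 15 or later, the offer opens on or after day 85. With discharge on day 10 it opens 5 days before day 85, too short a time to matter much. Only day 180 is materially exposed.

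**4. What the day-180 contrast estimates.** Let E be the effect of the early programme that persists at day 180, L the effect at day 180 of delayed exercise in a control who accepts, and u the share of controls who accept. Both effects are relative to no scheduled exercise. Then:

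- Expected day-180 difference = E − u × L
- Fraction of E retained = 1 − u × (L/E)

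The documents give neither u nor L/E. The table is an illustration under assumed values. The Calgary venue suggests that u is unlikely to go far above one half, which is about 6 of the 12 controls.

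| u (controls of 12) | L/E = 0 | L/E = 0.5 | L/E = 1 |
|---|---|---|---|
| 0 (0) | 100% | 100% | 100% |
| 0.25 (3) | 100% | 87.5% | 75% |
| 0.50 (6) | 100% | 75% | 50% |

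The sign reverses when u × L exceeds E. At u = 0.5 that needs L to be more than twice E. This is conceivable for physical activity: it is measured by an accelerometer worn for seven consecutive days, so sessions in a current programme would register directly, while E is what remains after about three months off programme. It is less plausible for immune recovery.

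**The case against.** The strongest reply is that the text describes an offer and nothing more. Its start date, length and uptake are not stated. The venue is in Calgary, and the section on the submaximal aerobic test expects about half of participants to live elsewhere. The plan itself keeps exercise-arm children from outside Calgary on a home-based programme only. Uptake is therefore probably partial and could be small. This stands: crossover is possible, not certain, and its size cannot be derived from the documents. A small uptake would not restore a clean contrast, however, because those who accept would be selected by residence and motivation.

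A second reply is that the plan speaks of a programme implemented early and never defines day 180 as exercise versus no exercise. A comparison with optional delayed exercise still says something about early implementation. This also stands, but the control arm is defined by the absence of scheduled exercise, and nothing in the article tells the reader that this definition lapses before the last visit.

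A third reply is that an analysis plan not shown here may deal with day 180. It could relabel the contrast or restrict the tests. It could not restore an unexercised comparison arm once children have taken up the offer, and the timing of the offer is a design decision that the article does fix.

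A reader might also infer that the sedentary-lifestyle question can no longer be answered. The documents do not support that. The Discussion does not tie this question to day 180, and physical activity is also measured at baseline, day 30 and day 85. What weakens is the claim that any difference lasts.

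**Conclusion.** The point holds for day 180. The offer to controls opens about 80 to 100 days before a visit meant to show the programme's impact after it has ended, and the described analysis does not separate that visit. The likely direction is towards no difference, with a possible reversal for physical activity. The size is unknown because uptake is not given. Under the illustrative assumptions, with uptake up to one half and delayed exercise no more effective at day 180 than early exercise, between none and half of the day-180 difference is lost.

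The conclusion rests on two readings: that completion of phase 2 means the matching time for a control child, and that at least some controls accept before day 180.

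A reader might infer that the trial's comparisons as a whole are compromised. They are not: the effect of phase 1 is assigned to day 30 and that of phase 2 to day 85, and both remain essentially clean. The problem is confined to the mid-term durability conclusion and to repeated-measures tests that include day 180. It should be fixed, and before any control is offered the programme, because accepted offers cannot be undone.

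**What to change.** Preferred: change the Control group section so that the programme is offered once each child's day-180 assessments are complete, and align the Study design text and the consent information with it. This takes about one sentence in each place. The cost is that controls wait about three more months for an optional programme, which could slightly affect consent or retention in a trial of 24 children at one centre.

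If the offer cannot move:

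- record for each control whether the offer was accepted, when exercise began and how much was done up to day 180;
- base exercise-versus-control tests on visits up to day 85;
- report day 180 separately, as early versus optional delayed exercise, and draw no exercise-versus-control conclusion from it.

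This alternative costs some extra data collection and gives up a clean test of whether the effect lasts.

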### Medical treatment – transplant protocol

High dose chemotherapy and autologous SCT will be performed for a given child as per the recommended therapy for a given disease and stage risk group. Only children receiving myeloablative conditioning will be eligible. Most children will have a history of Sarcoma, Lymphoma, Neuroblastoma or Germ cell tumor. Supportive care will be as per institutional practice.

### Sample size

Power calculations were derived using GPower 3.1 [19] The sample size/power calculation was based on relevant intervention literature [12,20,21] with natural killer cell activity as the primary outcome measure (Cohen’s d = .79). With an α of .05 and power of .80, a minimum sample size of 20 participants is required. To account for potential drop out, we will recruit an additional 20%, for a total of 24 participants.

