### Data analysis

The raw data analysis will be performed using SPSS (v. 20.0) and will include descriptive, correlations, and repeated measures analysis of variance (ANOVA). Specifically, for the primary and second objectives, correlations will be run to examine the degree of relationship between the variables, and planned doubly multivariate repeated measures ANOVA’s will be performed to examine group differences between the intervention and control group. Descriptive statistics will be conducted for demographics, medical variables, adherence to the program, and physical activity behavior using means, standard deviations, and ranges as appropriate. As was previously mentioned, the statistician will be blinded to participant condition.

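### The minimum of 20 participants for 80% power does not follow from the stated d = 0.79 and alpha of 0.05 in two parallel groups

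*Protocol article*

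**What the plan says.** The Sample size section says the calculation was made in GPower 3.1, drawing on earlier intervention studies, "with natural killer cell activity as the primary outcome measure (Cohen’s d = .79"). It continues: "With an α of .05 and power of .80, a minimum sample size of 20 participants is required". To allow for dropout, "we will recruit an additional 20%, for a total of 24 participants". The 20 is therefore a total, not a number per group. The Study population section gives the split: "12 patients will be assigned to an EX training program and 12 subjects will be assigned to a control group".

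The Sample size section does not name the test, its sidedness, the number of measurements or any within-child correlation. The Data analysis section states the intended comparison: "planned doubly multivariate repeated measures ANOVA’s will be performed to examine group differences between the intervention and control group".

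**The concern.** Cohen's d is the difference between two means in standard deviation units, and this is a 1:1 parallel-group trial. Read directly, the paragraph describes a two-sample comparison with 10 children per group, and at d = 0.79 that is far too few for 80% power.

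This is not a complaint about detail left to an analysis plan. The article prints both the inputs and the output, and they disagree.

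The Abstract and the Discussion present the trial as the source of preliminary data for a multisite study. A non-significant result read against a claimed 80% power would look like fair evidence that exercise does not help. Reusing the same calculation would also undersize the next trial.

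**Working it through.** **Inputs.** From Sample size: d = 0.79, alpha = 0.05, target power 0.80, stated minimum N = 20, recruited N = 24. From Study population: equal allocation, so 10 v 10 at the minimum and 12 v 12 as recruited. Sidedness is not stated; two-sided is taken as the convention and one-sided is also shown. All correlations below are assumptions.

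**1. Attempt to reproduce N = 20 with a two-sample t-test.** With n per group, the noncentrality is d × √(n/2) on 2n − 2 degrees of freedom.

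| n per group | Noncentrality | Two-sided power | One-sided power |
|---|---|---|---|
| 10 | 0.79 × √5 = 1.77 | 38.7% | 52.2% |
| 12 | 0.79 × √6 = 1.94 | 45.6% | 59.1% |
| 21 | 0.79 × √10.5 = 2.56 | 70.5% | 80.8% |
| 26 | 0.79 × √13 = 2.85 | 79.8% | 87.8% |
| 27 | 0.79 × √13.5 = 2.90 | 81.3% | 88.9% |

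So 80% power needs 27 per group (54 in total) two-sided, or 21 per group (42 in total) one-sided. The stated 20 is not reproduced. Solving instead for the effect that gives 80% two-sided power: d = 1.325 at 10 per group and 1.197 at 12 per group.

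**2. Between-group effect in a repeated-measures ANOVA.** Put f = d/2 = 0.395, m measurements and common within-child correlation r. The noncentrality is N × f² × m / (1 + (m − 1)r), on 1 and N − 2 degrees of freedom. Example for N = 20, m = 7, r = 0.5: 20 × 0.156 × 7 / 4 = 5.46.

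| m | r | Power, N = 20 | Power, N = 24 |
|---|---|---|---|
| 2 | 0.5 | 48.8% | 57.0% |
| 4 | 0.5 | 56.1% | 64.8% |
| 7 | 0.5 | 59.9% | 68.7% |
| 7 | 0.3 | 75.2% | 83.2% |
| 7 | 0.2 | 84.6% | 90.9% |
| 4 | 0.1 | 83.4% | 90.0% |

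Seven is the number of blood draws listed under Specimen collection. One of them is the baseline draw, which cannot carry a treatment effect. With the six later draws and r = 0.5, power is 59.0% at N = 20 and 67.8% at N = 24.

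**3. Adjustment for baseline (ANCOVA).** The effective d is 0.79 / √(1 − r²), with r now the correlation between baseline and outcome. At N = 20 this gives 48.8% at r = 0.5, 64.8% at r = 0.7 and 79.5% at r = 0.8 (effective d = 0.79/0.6 = 1.317).

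**4. Within-between interaction with f = 0.395.** The noncentrality is N × f² × m / (1 − r). With m = 2 and r = 0.3: 20 × 0.156 × 2 / 0.7 = 8.92, power 80.6%. With m = 4 and r = 0, power is 82.7%. These settings do return N = 20. But with two measurements and two groups, f = 0.395 means each cell departs by 0.395 SD from the additive pattern. The difference in change is then 4 × 0.395 = 1.58 SD, twice the stated d.

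**The case against.** The strongest reply is that the planned analysis is a repeated-measures ANOVA, so a t-test at one time point is the wrong yardstick. Much of this stands. Repeated sampling raises power, and a genuine group difference of 0.79 SD can reach about 80% at 20 participants: several measurements with within-child correlation of about 0.2 or less do it, and so does ANCOVA with a baseline correlation of about 0.8. It would therefore be wrong to say that 20 can come only from an interaction calculation. It would also be wrong to say that the trial's power simply is 39% or 46%.

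A reader might likewise infer that the trial is bound to miss a true effect of the planned size more often than it finds it. That holds for the two-sided single-time-point test. It does not hold for the one-sided version (52% and 59%) or for seven draws at r = 0.5 (60% and 69%).

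A reader might also fault the step from 20 to 24. The article adds 20% to 20, and 20 × 1.2 = 24 is right. It states no expected dropout rate, so there is nothing for the figure to contradict.

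Finally, the Discussion speaks of pilot data, which softens the consequence. It does not remove an explicit 80% power claim on a named primary outcome.

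What does not stand is the idea that repeated measures rescue the sentence as printed. Each route to 80% needs a favourable correlation or an effect scale that the article never gives.

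**Conclusion.** The power statement is wrong as written: d = 0.79, alpha 0.05 and 80% power do not give 20 participants in two parallel groups. On the direct reading (two-sided, one time point) power is about 39% at 10 v 10 and 46% at 12 v 12, and 80% power would need 54 children or a true d of about 1.2 to 1.3.

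For the planned repeated-measures analysis the power depends on correlations the article does not state. At an assumed r of 0.5 it is about 49% to 60% with 20 children and 57% to 69% with 24, over two to seven measurements. The documents do not show which settings were entered in the software, so the source of the 20 cannot be identified.

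**What to change.** Keep the 24 children and rewrite the sample-size paragraph in one of two ways.

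- If a repeated-measures or baseline-adjusted calculation was used, state the test, its sidedness, the number of measurements, the assumed correlation and the effect on that scale, so that 20 can be reproduced.
- Otherwise replace the 80% claim with the power the design has: about 39% to 46% at d = 0.79 for a two-sided single-time-point comparison, with a range over plausible correlations for the planned repeated-measures analysis.

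In either case, present the primary result as a pilot estimate with a 95% confidence interval, and say that a non-significant result is not to be read as no effect.

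The cost is wording in one section and a less favourable stated power. No extra patients or assessments are needed.
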